#### Conclusion

Considering the three concepts, we concluded that the Web-based intervention was to be recognized as being useful and easy to use. Participants stated that they were likely to participate; now they were familiar with the content and structure. To improve the navigation and menu of the intervention, numbers were added to each module in order to indicate the sequence of the modules **.**

### Study Design in Order to Measure the Effectiveness of the Newly Developed Web-Based Intervention

#### Design

To evaluate the Web-based self-management intervention, we have planned a randomized controlled trial with an intervention and a self-help control group and a 6-month follow-up period among adults in the Netherlands having a rheumatic disease. The control group will be put on a waiting list and will cross-over to the intervention after 6 months. Participants in the intervention group will be given access to the Web-based self-management intervention ReumaUitgedaagd! Both groups will receive usual care, based on the medical standard guidelines of the Dutch Association of Rheumatology [21], which also includes attention for self-management by the use of informational and educational materials that are normally used by patients to promote self-management. These materials are offered on the website of the Dutch Arthritis Foundation. Measuring the effectiveness means that we investigate whether there is an additional effect of the Web-based intervention in the intervention group on top of the care that is usually offered. The medical-ethical review board of the University Medical Center Utrecht in the Netherlands has approved the design and the procedures of this study.

#### Randomization

Randomization will take place after informed consent and completion of the goal-setting procedure, using a computerized application of the University Medical Center Utrecht. This is an automated process with no interference from the investigators. We will use a stratified block randomization to decrease the likelihood of imbalance between three conditions (arthritis, osteoarthritis, and soft-tissue rheumatism). After randomization, the participants will be informed by the researcher if they are assigned to the intervention or control group. The participants of the intervention group will then start with the Web-based self-management intervention and be asked to work through the intervention within 2 months.

#### Outcome Measurements

In this study individual outcome measures, generic outcome measures, and process outcomes measures will be collected, most of them via the Internet with questionnaires, self-reported by the participants. Demographic variables including age, sex, disease duration, diagnosis, marital status, current treatment, education level, work, and comorbidity at baseline will be collected in order to characterize the group of participants. The timeframe for collecting the outcome measures is displayed in Figure 2.

**Figure 2 figure2:**
[figure not shown]
Time frame and flow-chard study design.

##### Individual Outcomes: Goal Accomplishment

A crucial and novel aspect of this study is that the intervention is customized to the needs of the participant. This is one of the reasons why the change –progress toward– the main personal goal is chosen as the primary individual outcome measure. Studies show that on individual outcome measures the effect is larger than on generic outcome measures [22-24], which is not unexpected because many of the patients are already on a functional level of generic outcome measures; even more so, given that patients with psychopathology are excluded. The three personal goals that the patient wants to accomplish are in a telephone interview with the researcher checked according to the following criteria: (1) the individual goals are aligned to the content and overall aim of the self-management intervention, (2) the goals focus on ‘knowledge’ and ‘skills’, and (3) the participant feels that each goal is achievable. In addition, the participant is asked to prioritize these goals (the first goal being the most important goal). Progress on the highest priority personal goal is the primary outcome of the study. Evaluations of the second and third personal goals are also conducted as (secondary) individual outcome measures.

The personal goals are measured with a Web-based NRS. The participant is asked to indicate with a score from 0 to 10 on the NRS to what extent he or she achieved this goal. The content of the primary goal can differ per person but the rate of change can be compared between subjects because they are measured on the same scale.

##### Generic Outcomes

The following generic outcome measures are assessed (all self-reports): pain, disease activity, self-management skills, quality of life, and sick leave.

Self-reported pain and disease activity will be scored by the participant on a Web-based NRS from 0 to 10. The higher the score, the more pain or disease activity.

Self-management will be measured with the Dutch translation of the Web-based Health Education Impact Questionnaire (heiQ) [25], which consists of 40 questions with scores ranging from 1 (not at all true) to 4 (exactly true) and are organized into a set of eight scales: health-directed behavior, positive and active engagement in life, emotional well-being, self-monitoring and insight, constructive attitudes and approaches, skills and technique acquisition, social integration and support, and health navigation. In a recent study of patients with a chronic disease, the heiQ scales showed good internal consistency, with Cronbach’s alpha ranging from 0.70 to 0.89 on the eight independent scales, and high construct validity [26].

Quality of life will be assessed with the Web-based Medical Outcomes Study 12-item Short Form Health Survey (SF-12) [27], which includes eight questions on functional status, three questions on general well-being, and one question on general health. The psychometric properties of the SF-12 are good [27].

Sick leave is measured with three questions regarding (1) working in a paid job (yes/no/how many days a week), (2) sick leave during the past month, and (3) reasons for sick leave. Two measures of health care assumption are recorded as follows: self-reported visits to general practice, medical specialist, or physiotherapist, and whether or by whom support is offered to achieve the personal goals.

##### Process Outcomes

Feasibility is measured as a process outcome in the effectiveness study to evaluate the intervention in real-life in a larger group. Feasibility will be measured within the intervention group using the three concepts of the TAM [18,28] (see Textbox 1).

Use and adherence of the Web-based self-management intervention are digitally measured by Google Analytics within the intervention group. This was done by counting: (1) the number of starting and finishing participants within the time period, (2) the number of started and finished exercises, (3) the number of logins, (4) the number of messages that were put on the discussion board, (5) the number of contact moments with the expert trainers, and (6) the number of messages on the message box.

#### Power Calculation

To be able to compare our results with previous evaluations of self-management interventions, power calculation was based on the generic outcome parameters. In previous research, the generic measures of self-efficacy (which is close to our measurement of self-management skills) and functioning (which is part of our quality of life measurement), small to moderate effect-sizes (d) were found varying from 0.21 to 0.42 [11,29,30]. An effect-size d of 0.30 is similar to an effect-size f of 0.15 in repeated measures analysis of variance. In the current study, to be able to find a small to moderate difference (f=0.15) between the experimental and control groups using repeated measures analysis of variance, the total sample size needs to be N=90 (2 groups of n=45): G*Power3: f=0.15, 1-ß=.80, α=.05 two-tailed, r=.50, two groups, two repeated measures (baseline vs one post-therapy measurement) [31]. Taking a dropout rate of 25% into account, we decided to recruit 120 participants. The expectation of a small to moderate effect-size on these generic outcome measures may be explained because patients already have reasonable scores on self-management and quality of life at the start of the study. And there is little reason to expect that the intervention will affect other generic measures such as disease activity and sick leave.

As the crucial aspect of the current study is that the intervention is customized to the needs of the individual participant, the change on the main individual goal is chosen as primary outcome measure, and the change on the other two individual outcome measures (evaluation of the second and third personal goal) is considered important as well. Our sample size is large enough to examine differences in this primary outcome measure. Based on previous studies with individual outcome measures [22-24], we expect a moderate effect-size (d=0.5) for the control group and a large effect-size (d=1.2) for the intervention group resulting in a moderate to large (d=0.7, f=0.35) effect-size when comparing the intervention group and the control group using the three individual primary and secondary outcome measures. The calculated sample size is therefore considered to be safely chosen to test the main individual goal and both secondary individual outcome measures.

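### The d-to-f conversion behind N=90 does not fit the test that produces it: power for d=0.30 is about 29%, not 80%

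*Protocol article*

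**What the plan says.** All the relevant statements are in the Power Calculation section of the protocol article.

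- The sample size comes from the secondary, generic measures: "power calculation was based on the generic outcome parameters". For these, in earlier work, "small to moderate effect-sizes (d) were found varying from 0.21 to 0.42".
- The planning value is d=0.30, converted as follows: "An effect-size d of 0.30 is similar to an effect-size f of 0.15 in repeated measures analysis of variance".
- The aim is "to be able to find a small to moderate difference (f=0.15) between the experimental and control groups using repeated measures analysis of variance", with the settings "G*Power3: f=0.15, 1-ß=.80, α=.05 two-tailed, r=.50, two groups, two repeated measures (baseline vs one post-therapy measurement".
- The result is "the total sample size needs to be N=90 (2 groups of n=45", and then "Taking a dropout rate of 25% into account, we decided to recruit 120 participants".
- For the personal-goal outcomes the same halving is used, "resulting in a moderate to large (d=0.7, f=0.35) effect-size when comparing the intervention group and the control group", and the sample is declared safely large.

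The Statistical Analysis section plans a random-intercept linear mixed model with group, time and group × time. The G*Power test option is not named.

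**The concern.** Cohen's f is the standard deviation of the tested effects divided by the error SD, so its relation to d depends on which effect is tested. For two group means, f = d/2. For a 2 × 2 group × time interaction, a difference in change of d is spread over four cells and f = d/4. If d was halved as for the first test and the result entered into the second, the trial was sized for an effect twice as large as the one written down.

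The step matters because N=90, and so N=120, was derived from it. The stated purpose is comparison with earlier self-management evaluations on self-efficacy and functioning. A reader who trusts the 80% would take a non-significant heiQ or SF-12 result as fair evidence against an effect of d=0.30, when the trial would miss such an effect about seven times in ten.

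**Working it through.** **Inputs (Power Calculation section).** f=0.15, taken as d=0.30; two-sided α=.05; power .80; r=.50; two groups; m=2 measurements; N=90 (45 per group); 25% dropout.

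**Step 1: reproduce N=90.** For the repeated-measures interaction test,

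λ = f²·N·m/(1−r) = 0.0225 × 90 × 2 / 0.5 = 8.1, with df 1 and 88.

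Power is 0.804; at N=88 it is 0.795. So 90 is the smallest even N. The dropout step also reproduces: 90/0.75 = 120.

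**Step 2: check the other options.**

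| Test, f=0.15, r=.50, m=2 | Power at N=90 | N for 80% |
|---|---|---|
| Group × time interaction | 0.804 | 90 |
| Time effect (within factor) | 0.804 | 90 |
| Group effect (between factor), λ = f²·N·m/(1+(m−1)r) = 2.7 | 0.369 | 264 |

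The time effect does not compare groups. Among tests that do, only the interaction gives 90. It also matches the change-based outcome and the group × time term in the planned model.

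**Step 3: convert d for that test.** Suppose one group changes by d (in SD units) more than the other. After removing the main effects, the four cells are +d/4, −d/4, −d/4 and +d/4. Their standard deviation is d/4, so f = d/4.

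- f=0.15 corresponds to d = 4 × 0.15 = 0.60.
- d=0.30 corresponds to f=0.075, giving λ = 0.005625 × 90 × 2 / 0.5 = 2.025 and power 0.291.

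**Step 4: check without f.** The SD of change is σ√(2(1−r)), which equals σ at r=.50. A two-sample t test on change therefore uses d directly. Noncentrality is d√(n/2) with n=45 per group and 88 df.

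| d | Power, N=90 |
|---|---|
| 0.21 | 0.166 |
| 0.30 | 0.291 |
| 0.42 | 0.504 |
| 0.60 | 0.804 |
| 0.70 | 0.907 |

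The figures for 0.30 and 0.60 agree with Step 3. A simulation of 40,000 trials at d=0.30 gave 0.289. Power reaches 80% at d≈0.597.

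**Step 5: what d=0.30 would need.** The change analysis needs 352 completers (176 per group), or about 352/0.75 ≈ 470 recruited. With baseline adjustment, residual variance is 1−r² = 0.75 and the need is about 264 completers. If all 120 recruits were analysed, the change analysis would have 0.371.

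**Step 6: the primary outcome.** For d=0.7 the interaction value is f = 0.7/4 = 0.175, so λ = 0.030625 × 90 × 2 / 0.5 = 11.025 and power is 0.907. The stated f=0.35 would imply more than 0.999. The protocol gives no correlation for the goal rating. If r=.50 is replaced by assumed values, the change-analysis power is 0.79 at r=.30 and 0.99 at r=.70.

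**The case against.** The defence has four parts.

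*Halving d is standard, and one option does give 80% at N=90.* For the time effect, f = d/2 is correct: a pre–post change of 0.30 SD in 90 people at r=.50 has 80.4% power. But the protocol says the contrast is between the experimental and control groups, so this does not support the stated claim. Where halving is right for a group comparison, the requirement is 264.

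*The planned mixed model uses baseline, 3 and 6 months, not two measurements.* This stands in part. The 29% describes the calculation as stated. If all pairwise correlations are assumed to be .50, averaging both follow-ups against baseline gives 37% at d=0.30. Baseline adjustment with one follow-up also gives 37%, and with the mean of both follow-ups 51%; the article does not specify such adjustment. A higher correlation helps too: the change analysis has 44% at r=.70 and 60% at r=.80, and needs r near .9 to reach 80%. At the stated r=.50 none of these restores 80%.

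*The generic outcomes are secondary, and the primary conclusion survives.* True, and it limits the damage. But the protocol chose to derive its sample size from the generic outcomes, so the justification as written fails.

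*The protocol nowhere says it will read non-significance as no effect.* Also true. The risk lies with readers who rely on the stated power, and one sentence removes it.

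**Conclusion.** The power statement is wrong as written. N=90 is correct arithmetic for f=0.15 in a group × time test, but that f stands for d=0.60, not 0.30. At r=.50, with baseline and one follow-up, power for d=0.30 is 29% and the cited range is covered with 17% to 50%. The effect with 80% power, about 0.60, lies above that whole range. The 29% does not depend on whether d is scaled to the raw or the change SD, since these are equal at r=.50.

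The claim that the sample suffices for the primary goal outcome holds at d=0.7, with about 91% power. That figure rests on r=.50, which the protocol states only for the generic calculation, and on 0.7 being in units of the outcome SD. The margin is thinner than f=0.35 suggests.

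**What to change.** Keep N=120 and rewrite the Power Calculation section.

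1. Name the test (group × time interaction) and give its conversion, f = d/4. Replace f=0.35 by f=0.175 for d=0.7.
2. State that 90 completers give 80% power for a between-group difference in change of about d=0.60, and 29% for d=0.30. If a baseline-adjusted analysis is adopted, the figures are about d=0.52 (0.597 × √0.75) and 37%.
3. Base the sample-size justification on the primary goal outcome: 91% at d=0.7 (97% if baseline-adjusted), conditional on r=.50, with the range from 79% at r=.30 to 99% at r=.70 for the change analysis.
4. State that non-significant generic outcomes cannot be read as absence of a small-to-moderate effect, and report them with confidence intervals.

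The cost is a text correction and a less favourable stated power for the generic outcomes. No participants are added and the design does not change.

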#### Statistical Analysis

Demographic and disease-specific outcomes will be descriptively presented per group, where possible, with means and standard deviations. The Consolidated Standards of Reporting Trials statement [32] will be used to report the results of this study. Quantitative data will be entered into a SPSS database. Effect analyses will be done according to intention to treat analysis by means of linear mixed-models for longitudinal measurements with random intercept. Fixed effects for group, time, and group × time will be included in the model. Sick leave and health care use will be counted and differences between both groups will be analyzed using parametric tests or nonparametric tests, depending on the distribution of the data. Process outcomes, feasibility, use, and adherence will be analyzed with descriptive statistics.

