**Results:**

Considerations from self-determination theory and a comprehensive assessment of preferences and needs in patients with a rheumatic disease guided the development of the Web-based intervention. The usability study showed that the intervention was useful, easy to use, and accepted and appreciated by the target group of patients. The planned randomized controlled trial is designed to be conducted among 120 adults with a rheumatic disease, who are assigned to the self-management intervention or a self-help control group. Both groups will be asked to formulate personal goals they want to achieve concerning their self-management. Progress toward the personal goal is the primary outcome measure of this study. Self-reported Web-based measures will be assessed before randomization at baseline, and 3 and 6 months after randomization. Also, feasibility and adherence to the Web-based self-management intervention as process outcomes will be evaluated.

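### A random-intercept-only model over three visits can misstate the standard error of change from baseline in either direction; an unstructured covariance avoids this at little cost

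*Protocol article*

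**What the plan says.** The Statistical Analysis section specifies intention-to-treat effect analyses by "linear mixed-models for longitudinal measurements with random intercept" and adds: "Fixed effects for group, time, and group × time will be included in the model". It names no random slope, residual covariance structure or robust standard error. It also does not say whether the deciding test is the overall group-by-time interaction or a contrast at one visit.

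The Abstract (Results) gives three occasions: "Self-reported Web-based measures will be assessed before randomization at baseline, and 3 and 6 months after randomization". Under Individual Outcomes: Goal Accomplishment, the primary outcome is fixed as follows: "Progress on the highest priority personal goal is the primary outcome of the study". It is scored at each occasion on a 0 to 10 scale: "The participant is asked to indicate with a score from 0 to 10 on the NRS to what extent he or she achieved this goal".

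For the sample size, the Power Calculation section uses "α=.05 two-tailed" and "r=.50, two groups, two repeated measures (baseline vs one post-therapy measurement". That r=.50 is the only correlation in the article. No standard deviations are given for any visit.

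**The concern.** A random intercept with independent residuals is compound symmetry: equal variances at every visit and equal correlations between every pair of visits. With three visits, the model estimates one within-person variance and uses it for every change, whether from baseline to 3 months, baseline to 6 months, or 3 to 6 months.

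The design gives some reason to doubt that these changes are equally variable. The Modules and Randomization sections allow 2 months for the programme, so both follow-ups fall after it and no scheduled treatment lies between them. If patients respond unevenly and keep what they gained, change from baseline varies more than change between the follow-ups. Pooling would then make the standard error of change from baseline too small. Other patterns make it too large. Either error matters for a primary outcome defined as change: one gives too many false positives and intervals that are too narrow, the other loses power.

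**Working it through.** **The plan's own figure.** For the within-between interaction in repeated measures ANOVA, the noncentrality is λ = f²·N·m/(1−r). With f = 0.15, N = 90, m = 2 and r = .50, λ = 0.0225 × 90 × 2 / 0.5 = 8.1, and power is 0.804. At N = 88 power is 0.795, so N = 90 reproduces. Recruitment also reproduces: 90/(1 − 0.25) = 120. With two occasions there is only one pairwise difference, so the equal-correlation assumption cannot misstate its variance. The issue arises with the third visit.

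**Formulae (complete data, same covariance in both arms).** For visits j and k:

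- True variance of change: V(j,k) = σj² + σk² − 2·ρjk·σj·σk.
- Variance of any change under the random-intercept model: the mean of V(0,3), V(0,6) and V(3,6).
- SE ratio (model/true) = √(mean V / V of the contrast tested).
- Type I error ≈ 2·[1 − Φ(1.96 × SE ratio)].

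The model is therefore right for every contrast when the three difference variances are equal. Equal variances and equal correlations are sufficient for that, but not necessary.

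**Inputs.** Every covariance below is an assumption. Correlations are listed as 0–3 / 0–6 / 3–6 months.

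| SDs (0, 3, 6 mo) | Correlations | V(0,3), V(0,6), V(3,6) | Mean | SE ratio 3 mo; 6 mo | Type I error 3 mo; 6 mo |
|---|---|---|---|---|---|
| 1, 1, 1 | .5/.5/.5 | 1.0, 1.0, 1.0 | 1.000 | 1.00; 1.00 | 0.050; 0.050 |
| 1, 1, 1 | .5/.5/.7 | 1.0, 1.0, 0.6 | 0.867 | 0.931; 0.931 | 0.068; 0.068 |
| 1, 1, 1 | .4/.4/.7 | 1.2, 1.2, 0.6 | 1.000 | 0.913; 0.913 | 0.074; 0.074 |
| 1, 1, 1 | .4/.3/.7 | 1.2, 1.4, 0.6 | 1.067 | 0.943; 0.873 | 0.065; 0.087 |
| 1, 1, 1 | .5/.25/.5 (AR(1)) | 1.0, 1.5, 1.0 | 1.167 | 1.080; 0.882 | 0.034; 0.084 |
| 1, 1, 1 | .6/.6/.4 | 0.8, 0.8, 1.2 | 0.933 | 1.080; 1.080 | 0.034; 0.034 |
| 0.7, 1, 1 | .5/.5/.5 | 0.79, 0.79, 1.0 | 0.860 | 1.043; 1.043 | 0.041; 0.041 |
| 1.5, 2.5, 2.5 | .5/.5/.5 | 4.75, 4.75, 6.25 | 5.250 | 1.051; 1.051 | 0.039; 0.039 |
| 1.5, 2.5, 2.5 | .2/.2/.7 | 7.0, 7.0, 3.75 | 5.917 | 0.919; 0.919 | 0.072; 0.072 |
| 1.5, 2.5, 2.5 | .5/.5/.62 | 4.75, 4.75, 4.75 | 4.750 | 1.00; 1.00 | 0.050; 0.050 |

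Worked line for .4/.3/.7 at 6 months: mean V = (1.2 + 1.4 + 0.6)/3 = 1.067; SE ratio = √(1.067/1.4) = 0.873; type I error = 2·[1 − Φ(1.96 × 0.873)] = 0.087.

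**Simulation under the null, 45 per arm.** For .4/.3/.7 (6,000 runs), the 6-month contrast rejected in 0.089 of runs with the random intercept, against 0.051 when the change was tested with its own variance. Twelve assumed structures were run with 40,000 replicates each. AR(1) gave 0.032 at 3 months and 0.084 at 6 months, .4/.4/.7 gave 0.074 at both, and .6/.6/.4 gave 0.036 and 0.035. Over all twelve, the 2-df group-by-time test stayed between 0.051 and 0.058. Dropout was not modelled.

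**The case against.** The strongest reply is that the direction of the error is assumed. A reader might infer that the planned model understates the standard error and inflates the type I error. The article does not support that: it gives no three-visit covariance, and the same model is exact under some structures and conservative under others. This part of the reply stands.

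Two supporting arguments for inflation also fail. One is that goals not yet achieved would give narrow, low baseline scores. The article does not say they do; its goal criteria concern fit with the intervention, knowledge and skills, and achievability. A narrow baseline alone also works the other way: SDs of 1.5/2.5/2.5 with r=.5 throughout give an SE ratio of 1.05. Inflation to 0.072 with those SDs required baseline correlations of .2, well below the planned .50. The other argument is that harm is avoided only if all variances and correlations are equal. The last table row disproves it.

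Next, the article names a group-by-time effect and no single-visit contrast, and the overall test stays near nominal. This also stands and limits the point. The sample size was nevertheless set on change from baseline to one post-therapy measurement, and that is the kind of contrast exposed.

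Finally, a condensed article need not state the residual structure, and a full analysis plan may do so. That is fair. The point addresses the random structure the article does name, and it falls away if the full plan already sets a flexible covariance. Nor is there a basis for extending a direction of error to the generic outcomes, for which the article likewise gives no three-visit covariance.

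**Conclusion.** The concern holds in conditional form. Read with independent residuals, the stated model ties the standard error of every change to one common variance. If the pairwise difference variances are unequal, a single-visit change from baseline gets a standard error that is too small or too large. In the structures examined the SE ratio runs from 0.87 to 1.08 and the type I error from about 0.03 to 0.09 against a nominal 0.05. Inflation is mainly to be expected when the two post-intervention visits correlate more with each other than with baseline, or when correlation decays with time and the 6-month contrast is tested. The 2-df interaction test is little affected.

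These figures rest on assumed covariances, complete data and a common covariance in both arms. They show how far the standard error could be off; they do not show that this trial's test is inflated.

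**What to change.** In the Statistical Analysis section, replace the random intercept by an unstructured residual covariance over baseline, 3 and 6 months (SPSS MIXED, REPEATED subcommand, COVTYPE(UN)), estimated by REML with Satterthwaite or Kenward-Roger degrees of freedom. The fixed effects stay as they are. The unstructured matrix should replace the random intercept rather than be added to it, because it already contains the between-person variance.

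The cost is one line of text and four extra covariance parameters (six instead of two), which is negligible with about 120 participants and three fixed visits. The sample size calculation is unaffected, since it uses two occasions only.

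### The mixed model estimates a baseline group difference that randomisation already makes zero, so it tests raw change and gives up precision the baseline score could supply

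*Protocol article*

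**What the plan says.** All of this is in the protocol article.

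- **Model (Statistical Analysis).** Effects are analysed by intention to treat "by means of linear mixed-models for longitudinal measurements with random intercept", and "Fixed effects for group, time, and group × time will be included in the model". No baseline covariate is listed, and nothing constrains the arms to a common baseline mean.
- **Timing (Abstract, Results).** "Self-reported Web-based measures will be assessed before randomization at baseline, and 3 and 6 months after randomization".
- **Primary outcome (Individual Outcomes: Goal Accomplishment).** "Progress on the highest priority personal goal is the primary outcome of the study", scored on a 0 to 10 numeric rating scale and described as change on the main goal.
- **Sample size (Power Calculation).** The inputs are "G*Power3: f=0.15, 1-ß=.80, α=.05 two-tailed, r=.50, two groups, two repeated measures". Baseline counts as one of the two measures and a single later assessment as the other. The result is 90 in total, 45 per group, raised to 120 for 25% dropout. A separate paragraph expects d=0.7 between arms on the personal goals and judges the same sample ample for them.

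**The concern.** Read together, these sections put baseline in the response vector and let each arm have its own baseline mean. Because baseline precedes randomisation, the expected difference between those means is zero. Estimating it spends information on a known quantity, and the chance imbalance in the sample is subtracted in full from the follow-up difference. Randomisation is stratified by diagnosis only, so baseline goal scores are not balanced by design.

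At stake is the precision of the treatment effect on the primary outcome and on every other scale analysed this way, in a trial planned on 90 completers. The baseline score that would recover part of that precision is already being collected.

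**Working it through.** **Inputs.** From Power Calculation: f=0.15, two-sided α=0.05, r=.50, two groups, two measures, N=90, 25% dropout, and d=0.7 for the goals. My assumptions: equal baseline and follow-up SDs (set to 1) unless stated otherwise, complete data and categorical time.

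**1. Reproduce the plan's figure.** For the group × time test, the noncentrality is λ = f²·N·m/(1−r) = 0.0225 × 90 × 2 / 0.5 = 8.1, with 1 and 88 degrees of freedom. Power is 0.804, and 90 is the smallest even N that reaches 80%. Then 90/0.75 = 120. The between-group version of the calculation would need 264, so the stated N belongs to the change test.

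**2. Put that effect in SD units.** In a 2 × 2 layout the interaction f is a quarter of the difference in change, so f=0.15 corresponds to 4 × 0.15 = 0.6 SD. Check: (N/4) × 0.6² / [2(1−r)] = 22.5 × 0.36 / 1 = 8.1, the same λ. Whether 0.6 SD is what the plan meant by d=0.30 is a separate question, and the variance ratio below does not depend on it.

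**3. What the stated model estimates.** In 300 simulated trials (45 per arm, three visits, r=0.5) fitted with the stated model, the month-6 group × time estimate equalled the raw difference in mean change, with a largest gap of 4e-15. It correlated −0.49 with chance baseline imbalance. The constrained-baseline estimate correlated 0.00.

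**4. Variance comparison (per-person units).**

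- Raw change: 2(1−r), which is 1.00 at r=.50.
- Baseline-adjusted: 1−r², which is 0.75 at r=.50.
- Ratio: (1−r²)/[2(1−r)] = (1+r)/2 = 0.75.

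Generalised least squares with three visits and 45 per arm gives 0.0444 with a free baseline and 0.0333 with a constrained one, again a ratio of 0.75. The simulated ratio was 0.77. Confidence intervals narrow by 1 − √0.75, about 13%. For equal precision the change analysis needs 1/0.75 = 1.33 times the patients.

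**5. Power at r=.50, 45 per arm, one follow-up.**

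- Effect of 0.6 SD: λ goes from 8.1 to 22.5 × 0.36 / 0.75 = 10.8, and power from 0.80 to 0.90. N for 80% power falls from 90 to 68.
- d=0.7 in raw-score SDs: λ goes from 22.5 × 0.49 = 11.0 to 11.025/0.75 = 14.7, and power from 0.91 to 0.97.

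**6. Range over r (assumed), equal SDs, 0.6 SD effect, N=90.**

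| r | Variance ratio | Power, change | Power, adjusted |
|---|---|---|---|
| 0.2 | 0.60 | 0.61 | 0.82 |
| 0.3 | 0.65 | 0.66 | 0.84 |
| 0.5 | 0.75 | 0.80 | 0.90 |
| 0.7 | 0.85 | 0.95 | 0.98 |

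**7. Unequal SDs (assumed).** With follow-up SD 1 and baseline SD s, the change variance is 1 + s² − 2rs and the adjusted variance stays at 1−r².

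- s=0.75: ratios 0.76, 0.82 and 0.92 at r=.2, .3 and .5. For example, at r=.2, 0.96/1.2625 = 0.76.
- s=0.5: ratios 0.91, 0.96 and 1.00.

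The gain can therefore shrink to nothing.

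**The case against.** **The plan is coherent and valid as written.** The outcome is change, the model tests change, and N=90 was computed for a change test. Under randomisation the contrast is unbiased with correct type I error. Regression to the mean acts equally on both arms in expectation, and chance imbalance is already reflected in the standard error. All of this stands, and it limits the point to efficiency. It does not justify the free baseline term: in a randomised trial the constrained model estimates the same difference in mean change, with less variance under the conditions above.

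**This is a condensed article, and baseline handling may sit in an analysis plan.** Adjustment is not ruled out. But the article does more than stay silent: it names the fixed effects, and the point is about that stated choice.

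**A reader might go further and infer that the primary outcome falls below 80% power.** People choose goals they have not yet reached, so the baseline to follow-up correlation may be low. At d=0.7 and 45 per arm, change-analysis power is 79% at r=.3 and 74% at r=.2. The documents do not support that inference, because it needs several assumptions to hold at once:

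- r of .3 or below. The only r in the article is .50, given for the generic outcomes, and there power is 91%.
- Equal SDs. If unmet goals bunch baseline scores low, the baseline SD is probably smaller. At r=.2, .3 and .5, change-analysis power is 83%, 88% and 95% with a baseline SD of 0.75, and 89%, 92% and 97% with 0.5.
- d=0.7 in raw-score SDs. The article forms it as 1.2 − 0.5 and states no standardiser. In change-score SDs, power is 91% whatever r is.
- One follow-up and 45 per arm. Averaging months 3 and 6 under a persistent effect gives 85% at r=.2 and 89% at r=.3. With 60 per arm, one follow-up gives 85% and 90%.

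**Conclusion.** The point holds as an efficiency weakness in a stated model. At the plan's own r=.50 and with equal SDs, using the baseline score would cut the variance of the treatment effect by 25%. That is worth 80% to 90% power for the effect that N=90 detects, or 91% to 97% for d=0.7 with 45 per arm. The loss is partial. It grows at lower r, and shrinks as r approaches 1 or as the baseline SD falls below the follow-up SD. The article gives neither r nor the SDs for the goal rating, so the gain on the primary outcome itself cannot be fixed. No claim is made that the analysis is biased, that N=90 is wrong for the stated model, or that the primary outcome falls below 80% power. The identity with raw change is exact only for complete data and categorical time. With dropout the mixed model also uses incomplete records, but the baseline difference is still freely estimated.

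**What to change.** For the goal ratings, heiQ, SF-12, pain and disease activity, replace the stated fixed effects with one of these:

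- **Baseline as covariate.** Model months 3 and 6 with group, visit, group × visit, baseline score and baseline × visit.
- **Constrained longitudinal model.** Keep all three visits as responses, fit a common baseline mean (no group term at baseline), and include group × visit terms at months 3 and 6. Use an unstructured covariance across visits instead of only a random intercept. Otherwise the implied adjustment slope is wrong if variances differ between visits.

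The two are close but not identical when data are missing, so one should be named in advance, before outcomes are examined by arm. The cost is a sentence or two of analysis wording, with no new data and no change to the sample size.
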